### 16.2 Post-operative morbidity score (POMS)

Post-operative morbidity according to the post-operative morbidity score (45)

| Morbidity type | Criteria                                                                                                                 | Source of data      |
|----------------|--------------------------------------------------------------------------------------------------------------------------|---------------------|
| Pulmonary      | Has the patient developed a new requirement for oxygen or respiratory support?                                           | Patient observation |
|                |                                                                                                                          | Treatment chart     |
| Infectious     | Currently on antibiotics and/or has had a temperature of >38°C in the last 24 hr.                                        | Treatment chart     |
|                |                                                                                                                          | Observation chart   |
| Renal          | Presence of oliguria <500 mL/24 hr; increased serum creatinine (>30% from preoperative level); urinary catheter in situ. | Fluid balance chart |
|                |                                                                                                                          | Biochemistry result |
|                |                                                                                                                          | Patient observation |

| Morbidity type   | Criteria                                                                                                                                                                                                                                                                                                       | Source of data      |
|------------------|----------------------------------------------------------------------------------------------------------------------------------------------------------------------------------------------------------------------------------------------------------------------------------------------------------------|---------------------|
| Gastrointestinal | Unable to tolerate an enteral diet for any reason including nausea, vomiting, and abdominal distension (use of antiemetic).                                                                                                                                                                                    | Patient questioning |
|                  |                                                                                                                                                                                                                                                                                                                | Fluid balance chart |
|                  |                                                                                                                                                                                                                                                                                                                | Treatment chart     |
| Cardiovascular   | Diagnostic tests or therapy within the last 24 hr for any of the following: new myocardial infarction or ischemia, hypotension (requiring fluid therapy >200 mL/hr or pharmacological therapy), atrial or ventricular arrhythmias, cardiogenic pulmonary oedema, thrombotic event (requiring anticoagulation). | Treatment chart     |
|                  |                                                                                                                                                                                                                                                                                                                | Note review         |
|                  |                                                                                                                                                                                                                                                                                                                |                     |
| Neurological     | New focal neurological deficit, confusion, delirium, or coma.                                                                                                                                                                                                                                                  | Note review         |
|                  |                                                                                                                                                                                                                                                                                                                | Patient questioning |
| Haematological   | Requirement for any of the following within the last 24 hr: packed erythrocytes, platelets, fresh-frozen plasma, or cryoprecipitate.                                                                                                                                                                           | Treatment chart     |
|                  |                                                                                                                                                                                                                                                                                                                | Fluid balance chart |
| Wound            | Wound dehiscence requiring surgical exploration or drainage of pus from the operation wound with or without isolation of organisms.                                                                                                                                                                            | Note review         |
|                  |                                                                                                                                                                                                                                                                                                                | Pathology result    |
| Pain             | New postoperative pain significant enough to require parenteral opioids or regional analgesia.                                                                                                                                                                                                                 | Treatment chart     |
|                  |                                                                                                                                                                                                                                                                                                                | Patient questioning |

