### 2.5.1 Definition of secondary outcome measures

Post-operative complications: Assessed with Clavien-Dindo classification up to 30 days postoperatively (44).

Post-operative morbidity: Will be assessed by the postoperative morbidity score (POMS) on postoperative day 3 and 5 (45).

Quality of recovery (QoR): Will be assessed the day before surgery and 3 days after surgery with the QoR-15 questionnaire (46, 47).

Overall survival: Survival time is calculated from the date of randomization to the date of death (all-cause), or for patients still alive to the date of last clinical follow-up or contact.

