Post-operative management: All women will be managed in a high-dependency post-operative care unit overnight as appropriate. An epidural infusion containing Ropivacaine 2 mg/ml and Sufentanil 1µg/ml will be administered continuously as per hospital routine (usually 4-14 ml/hour for 3 to 5 days after surgery) for pain management. In case of pain not relieved by epidural analgesia, nurse-controlled intravenous morphine or morphine equivalent as per hospital routine (usually 1-2 mg). Additionally, ten ml of the Ropivacaine 0.2% or 0.9% saline (depending on group allotment) will be injected intermittently every other hour through a bacterial filter and via an infusion pump (CADD-Solis) for 72 h postoperatively. The patients will be transferred to the general ward or later rehabilitation until ready for home discharge, which usually occurs on postoperative day 6 - 14, according to hospital routines. Patients will be followed-up via the hospital journal for later assessment of death at 3- or 5 years after surgery according to existing hospital routines.

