## **6 Routine anesthesia and surgery**

Anesthesia: All patients will be given premedication and intraoperative anesthesia according to standardized protocol at all the participating hospitals. A thoracic epidural will be inserted usually at the Th9-Th11 level before induction of general anesthesia. Usually, during surgery, 0.5% Ropivacaine 3-5 mL/hours will be used for pain management. Intravenous injection of Propofol and Remifentanil or equivalent will be used for induction of anesthesia Maintenance of anesthesia is a combination of epidural and inhalation anesthesia during the surgical

procedure and supplemented with infusion of Remifentanyl or equivalent if needed. To achieve neuromuscular blockade Rocuronium or equivalent will be used and will be monitored with train of four. Mechanical ventilation with oxygen in air will be used. Monitoring will include: arterial radial line, oxygen saturation and ECG monitoring. If needed, goal-directed therapy and invasive monitoring guidance will be used to standardize intraoperative fluid management. Mean arterial pressure will be maintained above 65mmHg. Cardiac index >2.5 or stroke volume variation <15% will be the cut-off for hemodynamic instability and will be treated with fluid substitution. Hypotension will be treated with norepinephrine infusion if needed.

Surgery: Will be performed by as per clinical routine. The study treatment will not interfere with any part of the surgical treatment. If per-operative evaluation excludes the patients from cytoreductive surgery because disease extent and the abdomen is closed without any resection of tumor, the participant is excluded from the IPLA-OVCA trial.

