### 8.3 Data analyses

The primary endpoint, time to start of adjuvant chemotherapy will be analyzed using a linear regression model including the variable treatment. Results will be presented as the mean difference in days together with 95% confidence intervals and a Wald-test p-value. The significance level in the main analysis is set to 5%. Regression models including different clinical factors will also be estimated to take potential confounding into account. All analyses of primary and secondary outcome will be performed according to the intention-to-treat principle but may also be presented as per-protocol. For safety data, patients will be analyzed according to per-protocol approach.

Differences in complications, morbidity and in cardiac and renal impairment will be tested using Chi-square tests of independence. For dichotomous outcomes result will also be presented as differences in proportions together with 95% confidence intervals. Overall survival time will be calculated from the date of randomization to the date of death. For patients still alive, survival time will be calculated from the date of randomization to the date of last visit. Results from the survival analysis will be graphically presented as Kaplan-Meier curves. Proportional hazards regression models will be used to estimate the effect of the intervention on time to death. Results will be presented as hazard ratios 95% confidence intervals and Wald test p-values.

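### Day-3 POMS may record the routine epidural rather than recovery, and the chi-square test in 8.3 discards the order of the Clavien-Dindo grades

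*Protocol*

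**What the plan says.** **POMS.** Protocol 2.5.1 defines post-operative morbidity: "Will be assessed by the postoperative morbidity score (POMS) on postoperative day 3 and 5". Appendix 16.2 lists nine morbidity types. The pain type is positive for "New postoperative pain significant enough to require parenteral opioids or regional analgesia", with the treatment chart as its first data source. The renal type counts, among other criteria, "urinary catheter in situ".

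**Analgesia.** Section 6 states: "A thoracic epidural will be inserted usually at the Th9-Th11 level before induction of general anesthesia". Section 5.3 adds that an epidural infusion of ropivacaine and sufentanil "will be administered continuously as per hospital routine (usually 4-14 ml/hour for 3 to 5 days after surgery". Section 4.3 excludes women with a contraindication to epidural anesthesia. Rescue in both groups is intravenous morphine (5.3 and 10.6), a parenteral opioid.

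**Analysis.** Section 8.3 states: "Differences in complications, morbidity and in cardiac and renal impairment will be tested using Chi-square tests of independence". It adds that dichotomous outcomes will also be shown as differences in proportions with 95% confidence intervals, but does not say which outcomes are dichotomous. Appendix 16.1 sets out Clavien-Dindo as ordered grades I to V. Section 2.5.1 gives a 30-day window and no grade cut-off.

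**The concern.** A morbidity endpoint should differ between arms when recovery differs. Here one of the nine POMS items can be switched on by an analgesic technique planned for everyone in both arms, and the first reading falls on a day when that technique is usually still running. A composite that is positive as soon as any item is positive would then be positive in nearly everyone. A null day-3 result would reflect the analgesic routine and would not be evidence that recovery is the same.

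The Clavien-Dindo issue is separate. A chi-square test of independence gives the same answer however the grades are ordered and spreads its power over several degrees of freedom. A treatment that shifts patients towards milder complications produces an ordered difference, which this test is poorly placed to detect.

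**Working it through.** **1. The protocol's own figure, to fix the group sizes.** From 8.4: difference 5 days, SD 12, two-sided 5%, power 80%.

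n per arm = 2 × [12 × (1.960 + 0.842) / 5]² = 2 × 6.724² = 90.4, rounded up to 91, so 182 in total, as stated. The target of 220 is 110 per arm. The checks below use 91 to 110 per arm. The protocol gives no event rates or power for POMS or Clavien-Dindo, so every rate below is an assumption.

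**2. POMS on day 3 as any item positive.** Let f be the share of patients, equal in both arms, whose pain item is positive through the routine epidural. Let p be the rate of any other item being positive. If the two are independent, the observed rate is f + (1 − f)p. Assume p = 60% against 40%.

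Power = Φ[(d − 1.96·SE₀) / SE₁], with SE₀ from the pooled and SE₁ from the separate variances. For f = 90% and 91 per arm:
- rates 0.96 and 0.94, so d = 0.02
- SE₀ = √(0.95 × 0.05 × 2/91) = 0.0323
- SE₁ = √[(0.96 × 0.04 + 0.94 × 0.06)/91] = 0.0323
- power = Φ[(0.02 − 0.0633)/0.0323] = Φ(−1.34) = 9%

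| f | Observed rates | Power, 91 per arm | Power, 110 per arm |
|---|---|---|---|
| 0% | 60% v 40% | 77% | 85% |
| 50% | 80% v 70% | 34% | 40% |
| 80% | 92% v 88% | 14% | 17% |
| 90% | 96% v 94% | 9% | 10% |
| 95% | 98% v 97% | 6% | 7% |
| 100% | 100% v 100% | no test possible | no test possible |

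An epidural that usually runs 3 to 5 days covers day 3 in most patients but day 5 only in part. If the routine epidural is scored, f would be high on day 3 and lower, by an unknown amount, on day 5.

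**3. Clavien-Dindo.** Assumed control distribution none/I/II/III/IV/V: 30/20/30/12/6/2%. A common odds ratio of 0.5 halves the odds of being at or above each grade:
- any complication: odds 0.70/0.30 = 2.333, halved to 1.167, so 70% becomes 53.8%
- grade II or higher: odds 1, halved to 0.5, so 50% becomes 33.3%
- grade III or higher: odds 0.25, halved to 0.125, so 20% becomes 11.1%

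Simulated power at two-sided 5%, each range running from 91 to 110 per arm (allow about two points for simulation error):

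| Test | Odds ratio 0.5 | Odds ratio 0.6 |
|---|---|---|
| Unordered chi-square on all grades | 46-55% | 26-32% |
| 2x2 chi-square (any, II or higher, III or higher) | 39-70% | 25-48% |
| Wilcoxon rank-sum | 72-81% | 48-57% |

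Within the 2x2 row at odds ratio 0.5, cutting at any complication or at grade II or higher gives 61-62% at 91 per arm and 70% at 110. Cutting at grade III or higher gives 39-45%.

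**4. Sensitivity to the assumed grades.** Three further control distributions were tried: 25/20/30/10/8/5/1/1% and 10/25/40/10/8/5/1/1% (with III and IV split into a and b), and 30/25/25/12/5/3%. With a twofold reduction in odds, unordered chi-square has 41-55% power, grade III or higher 37-52%, and Wilcoxon 73-81%. With a 1.5-fold reduction, unordered chi-square has 12-21% and Wilcoxon 32-39%. With a 2.5-fold reduction, they have 67-82% and 92-97%.

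**The case against.** The strongest reply is that the protocol does not fix the endpoint criticised here. Nowhere does it say that POMS is analysed as any item positive. Chi-square tests could be run by morbidity type, which would leave eight of the nine types untouched by the pain item, and the summary may be given in a statistical analysis plan not available here. A pre-planned epidural is also not obviously new pain that requires regional analgesia. Pain is captured separately through numeric ratings (11.2), morphine use (10.6) and days with an epidural catheter (6.1). All of this stands, and it makes the POMS point conditional. It does not remove it. The items, the assessment days, the epidural routine and the test are all fixed in the protocol, any/none is the natural binary form for that test, and without a scoring rule two assessors can score the same patient differently.

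For Clavien-Dindo, the sentence on dichotomous outcomes allows a 2x2 test with one degree of freedom, for which ordering is not an issue. That also stands, but each cut-off examined still has less power than the Wilcoxon test under the assumed shift.

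A reader might go further and infer that POMS is near 100% in both arms by design, or that both secondary endpoints have little ability to show an effect. The documents do not support that. Saturation needs both the any-positive summary and the routine epidural being scored. Day 5 is only partly exposed. The unordered chi-square on Clavien-Dindo reaches 67-82% power for a 2.5-fold reduction in odds.

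**Conclusion.** The point holds in a conditional form for POMS and as a matter of efficiency for Clavien-Dindo.

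- **POMS:** if it is summarised as any item positive and the planned epidural counts, day 3 carries almost no information on recovery. Under the assumed 60% v 40% in the other items, power falls from 77-85% to 10% or less once 90% of patients are positive through the epidural. Day 5 is affected less, by an amount the protocol does not allow one to quantify.
- **Clavien-Dindo:** at an odds ratio of 0.5, the unordered test gives up about 26 points of power against a Wilcoxon test (46% v 72% at 91 per arm, 55% v 81% at 110). A 2x2 test loses between about 10 and 36 points, depending on cut-off and group size (at 91 per arm, 72% v 62%; at 110, 81% v 45%).

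The Clavien-Dindo figures rest on assumed grade distributions and a common odds ratio across grades, the setting in which a rank test does well. Both are secondary endpoints with no stated power target, and the primary endpoint is unaffected. The change is worth making, but the trial does not depend on it.

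**What to change.** In Protocol 2.5.1 and 8.3:

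1. State whether a routine, planned epidural scores the POMS pain item.
2. Analyse POMS by domain, and as any-positive or a count without the pain domain, on days 3 and 5. Report the pain domain and the standard total alongside.
3. Check, without reference to treatment arm, whether the urinary-catheter criterion in the renal domain saturates in the same way. If it does, excluding pain alone will not restore the composite.
4. Test the worst Clavien-Dindo grade within 30 days with a Wilcoxon test stratified by centre, with a proportional-odds estimate. Keep grade III or higher as a difference in proportions with a 95% confidence interval.

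**Cost.** This is a small wording amendment, because 8.3 names the test, and it should be made before unblinding. No treatment or visit changes. Section 6.1 says only that POMS is recorded, so confirm that the case report form holds the individual domains; if it does not, they must be taken from the source records. The pain-excluded summary is less comparable with the published total, which is why the total should still be reported.

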## 16.3 FIGO-staging

2014 FIGO ovarian, fallopian tube, and peritoneal cancer staging system and corresponding TNM (7).

| I         | Tumor confined to ovaries or fallopian tube(s)                                                                                                                                                                                                                                                                                                                                                                                 | T1                               |
|-----------|--------------------------------------------------------------------------------------------------------------------------------------------------------------------------------------------------------------------------------------------------------------------------------------------------------------------------------------------------------------------------------------------------------------------------------|----------------------------------|
| IA        | Tumor limited to one ovary (capsule intact) or fallopian tube, No tumor on ovarian or fallopian tube surface No malignant cells in the ascites or peritoneal washings                                                                                                                                                                                                                                                          | T1a                              |
| IB        | Tumor limited to both ovaries (capsules intact) or fallopian tubes
No tumor on ovarian or fallopian tube surface
No malignant cells in the ascites or peritoneal washings                                                                                                                                                                                                                                                | T1b                              |
| IC        | Tumor limited to one or both ovaries or fallopian tubes, with any of the following:
IC1 Surgical spill intraoperatively
IC2 Capsule ruptured before surgery or tumor on ovarian or fallopian tube surface
IC3 Malignant cells present in the ascites or peritoneal washings                                                                                                                                           | T1c                              |
| II        | Tumor involves one or both ovaries or fallopian tubes with pelvic extension (below pelvic brim) or peritoneal cancer (Tp)                                                                                                                                                                                                                                                                                                      | T2                               |
| IIA       | Extension and/or implants on the uterus and/or fallopian tubes/and/or ovaries                                                                                                                                                                                                                                                                                                                                                  | T2a                              |
| IIB       | Extension to other pelvic intraperitoneal tissues                                                                                                                                                                                                                                                                                                                                                                              | T2b                              |
| III       | Tumor involves one or both ovaries, or fallopian tubes, or primary peritoneal cancer, with cytologically or histologically confirmed spread to the peritoneum outside the pelvis and/or metastasis to the retroperitoneal lymph nodes                                                                                                                                                                                          | T3                               |
| IIIA      | Metastasis to the retroperitoneal lymph nodes with or without microscopic peritoneal involvement beyond the pelvis                                                                                                                                                                                                                                                                                                             | T1,T2,T3aN1                      |
| IIIA1     | Positive retroperitoneal lymph nodes only (cytologically or histologically proven)                                                                                                                                                                                                                                                                                                                                             |                                  |
| IIIA1(i)  | Metastasis ≤ 10 mm in greatest dimension (note this is tumor dimension and not lymph node dimension)                                                                                                                                                                                                                                                                                                                           | T3a/T3aN1                        |
| IIIA1(ii) | Metastasis > 10 mm in greatest dimension                                                                                                                                                                                                                                                                                                                                                                                       |                                  |
| IIIA 2    | Microscopic extrapelvic (above the pelvic brim) peritoneal involvement with or without positive retroperitoneal lymph nodes                                                                                                                                                                                                                                                                                                    | T3a/T3aN1                        |
| IIIB      | Macroscopic peritoneal metastases beyond the pelvic brim ≤ 2 cm in greatest dimension, with or without metastasis to the retroperitoneal lymph nodes                                                                                                                                                                                                                                                                           | T3b/T3bN1                        |
| IIIC      | Macroscopic peritoneal metastases beyond the pelvic brim > 2 cm in greatest dimension, with or without metastases to the retroperitoneal nodes (Note 1)                                                                                                                                                                                                                                                                        | T3c/T3cN1                        |
| IV        | Distant metastasis excluding peritoneal metastases
Stage IV A: Pleural effusion with positive cytology
Stage IV B: Metastases to extra-abdominal organs (including inguinal lymph nodes and lymph nodes outside of abdominal cavity) (Note 2)
(Note 1: includes extension of tumor to capsule of liver and spleen without parenchymal involvement of either organ)
(Note 2: Parenchymal metastases are Stage IV B) | Any T, Any N,
M1
T3c/T3cN1 |

